#### Sample size

3.1.8

The sample calculation was performed based on previous studies presented in the literature,^[37]^ considering the expected difference and standard deviation, weighting the CFU (bacterial colony forming units) variable. For the statistical calculation, paired samples were considered: α = 1.96 (5%); β = 0.84 (20%); test power 80%. The minimum number for this clinical trial per group was 16 teeth. 
[figure not shown]

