#### Experimental groups

3.1.9

Forty-eight teeth of healthy 6 to 12-year-old children of both genders, without distinction of race or ethnicity in the clinic of the dentistry course of Nove de Julho University (São Paulo, Brazil) will be select.

The participants will be allocated in the experimental groups as follows:

Group 1—PDT + atraumatic restaurative treatment (ART) (n = 24): for the PDT the PapacarieMblue (Fórmula e Ação) will be used. It will be left for 5 minutes in the cavity. The carious tissue will be removed and the application of the PapacarieMblue will be repeated. The tissue will then be irradiated in a single spot with a red laser, of wavelength of 660 nm, for 60 seconds, with the energy of 6J. These parameters were also applied in the vestibular root of the teeth, to try and prevent sensitivity. Laser parameters can be found in item 3.1.10. Selective removal of carious tissue will be made with a curette, followed by cavity cleaning and restoration with Riva Self Cure/HV – SDI.

Group 2—Atraumatic restaurative treatment (ART) (n = 24): Removal of infected dentin with a curette only, followed by cavity cleaning and restoration with Riva Self Cure/HV – SDI.

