#### Evaluation of dentin sensitivity—primary outcome

3.1.12

Before removal of the carious dentin, Group 1 and Group 2 volunteers will respond to the Visual Analogue Scale (VAS),^[38]^ which will obey the following protocol: gauze isolation of neighboring teeth; light air jet in the tooth with MIH for 2 seconds; sensitivity evaluation through the VAS scale. This sequence will be repeated at the end of the procedure, after insertion of the glass ionomer cement.

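### The sample size is set on paired CFU data, but the primary comparison is VAS sensitivity between two separate groups, so the stated 80% power does not apply to it

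*Protocol article*

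**What the plan says.** Section 3.1.8 (Sample size) gives the sizing variable and the data structure together: "weighting the CFU (bacterial colony forming units) variable. For the statistical calculation, paired samples were considered". The constants are 1.96 for a two-sided 5% level and 0.84 for 80% power, and the result is: "The minimum number for this clinical trial per group was 16 teeth". The expected difference and SD are mentioned without values in the readable text; they may stand in the figure that is not shown.

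Section 3.1.12 is headed "Evaluation of dentin sensitivity—primary outcome". It has both groups rate sensitivity on the VAS after an air jet, before caries removal and again after the restoration is placed.

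Section 3.1.9 (Experimental groups) sets out two arms of 24 teeth: "The participants will be allocated in the experimental groups as follows". The abstract describes patients randomly divided into two groups, the inclusion criteria (3.1.5) ask for one qualifying molar, and the specific objective (3.1.2) is to compare aPDT with ART. No split-mouth or matched design is described.

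**The concern.** The sizing basis differs from the primary comparison in two ways.

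- **Outcome.** The calculation is for CFU; the primary outcome is VAS. The hypotheses in 3.1.2 make the gap plain. The null hypothesis there already grants that PDT lowers the bacterial count and denies only the effect on sensitivity. Sensitivity is what separates the two hypotheses, and the calculation was not made for it.
- **Structure.** A paired calculation suits a before-after change within a tooth. It does not suit a contrast between teeth in different arms.

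A reader will naturally attach the 80% to the declared primary outcome. If the VAS comparison then shows no difference, the result could be read as evidence against a desensitising effect from a trial with known good power, when its ability to detect a VAS difference has not been stated.

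**Working it through.** **Inputs from the protocol article.** z-values 1.96 and 0.84 (sum 2.80) and n = 16 per group (3.1.8); 24 per group (3.1.9). No CFU or VAS difference or SD is readable.

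**1. Can 16 be reproduced?** Not forwards, since the difference and SD are not readable. It can only be back-solved, and the constants fit two formulas:

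- One-sample paired: n = (2.80 / d)², so d = 2.80 / √16 = 0.70 SDs of the paired differences (up to 0.72 if n was rounded up from just above 15).
- Two independent groups: n = 2 × (2.80 / d)², so d = 2.80 × √(2/16) = 0.99 SD (up to 1.02 with rounding).

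The text says paired, which points to the first, but the figure that could confirm it is not shown. The number 16 is neither confirmed nor refuted.

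**2. What would a paired 0.70 mean between groups? (illustration)** Assume that the paired formula was used, that the same raw difference applies between arms, and that arms are compared on post-treatment values. With pre-post correlation ρ, the SD of a paired difference is SD × √(2(1−ρ)), so the between-group standardised difference is d = 0.70 × √(2(1−ρ)). Power at 24 per group is Φ(d × √(24/2) − 1.96):

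| ρ (assumed) | d | Power, normal | Power, t-based |
|---|---|---|---|
| 0 | 0.99 | 93% | 92% |
| 0.3 | 0.83 | 82% | 80% |
| 0.5 | 0.70 | 68% | 66% |
| 0.7 | 0.54 | 47% | 45% |

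The stated 80% lies inside this range, so not even the direction of the discrepancy is fixed. These figures concern an unknown CFU effect and say nothing about VAS.

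**3. What can be said about VAS?** Without a VAS difference or SD, only the detectable standardised difference at the planned size:

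- Normal approximation: 2.80 × √(2/24) = 0.81 SD.
- t-based: 0.83 SD.
- With adjustment for baseline VAS and an assumed pre-post correlation of 0.5, multiply by √(1 − 0.5²) = 0.866: 0.70 SD (normal) or 0.72 SD (t-based).

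**The case against.** The strongest reply is that the formula has not been seen. The figure is missing from the text, the constants fit either formula, and 16 per group also matches an independent-group difference of 0.99 SD, at which 24 per group would give about 93% power. CFU is not incidental either: the alternative hypothesis names decontamination as well as desensitisation, and dentin is sampled before and after treatment in each tooth, for which a paired calculation is natural. Section 3.1.8 does not itself claim 80% power for VAS, and 24 exceeds the stated minimum by half.

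Much of this stands, and it rules out several stronger readings. A reader might infer that the calculation left out the factor 2 and that the trial needs 32 per group, twice the stated 16: 2 × (2.80/0.70)² = 32. That reuses the back-solved paired 0.70 as a between-group effect, which under the post-value comparison above is right only at a correlation of 0.5, and it presumes an unseen formula. A reader might also see a contradiction between 16 and 24. There is none, because 16 is given as a minimum, and the reason for the margin is a detail that an article may leave to the full protocol.

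What the reply does not remove is the mismatch itself. Both halves are in readable text. No content of the missing figure could make CFU the declared primary outcome or turn two separately allocated groups into pairs.

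**Conclusion.** The point holds as a mismatch between the sizing basis and the primary comparison. The 80% power and the minimum of 16 in 3.1.8 refer to paired CFU data and cannot be carried over to VAS sensitivity compared between aPDT and ART. No arithmetic error is shown, and underpowering is not shown.

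The power for VAS is undetermined. The one figure that does not depend on the missing CFU inputs is that 24 per group gives 80% power for a difference of about 0.81 SD (0.83 t-based), taking two independent groups, a two-sided 5% level and one analysed tooth per child. Whether a difference of that size is plausible or clinically relevant cannot be judged from the documents. The 45% to 93% range is an illustration under the assumptions stated with it, not an estimate of this trial's power.

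**What to change.** Rewrite 3.1.8 for the planned design, for example: with 24 teeth per group and a two-sided 5% level, the trial has 80% power for a between-group VAS difference of about 0.83 SD (t-based), or about 0.72 SD if the analysis adjusts for baseline VAS and the pre-post correlation is 0.5, which is an assumption. Then:

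- translate that difference into VAS units with a stated SD and its source, and say whether it is a difference worth detecting;
- delete the paired CFU calculation, or keep it labelled as a within-tooth before-after calculation for a secondary outcome, with the 80% attached to that only.

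The cost is one rewritten paragraph and a sourced VAS SD. No extra teeth are needed, and treatment and allocation do not change. The downside is a less favourable stated figure. A detectable difference also describes what 24 per group can show; it does not by itself justify 24.

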**Figure d35e768:**
[figure not shown]

#### Experimental groups

3.1.9

Forty-eight teeth of healthy 6 to 12-year-old children of both genders, without distinction of race or ethnicity in the clinic of the dentistry course of Nove de Julho University (São Paulo, Brazil) will be select.

The participants will be allocated in the experimental groups as follows:

Group 1—PDT + atraumatic restaurative treatment (ART) (n = 24): for the PDT the PapacarieMblue (Fórmula e Ação) will be used. It will be left for 5 minutes in the cavity. The carious tissue will be removed and the application of the PapacarieMblue will be repeated. The tissue will then be irradiated in a single spot with a red laser, of wavelength of 660 nm, for 60 seconds, with the energy of 6J. These parameters were also applied in the vestibular root of the teeth, to try and prevent sensitivity. Laser parameters can be found in item 3.1.10. Selective removal of carious tissue will be made with a curette, followed by cavity cleaning and restoration with Riva Self Cure/HV – SDI.

Group 2—Atraumatic restaurative treatment (ART) (n = 24): Removal of infected dentin with a curette only, followed by cavity cleaning and restoration with Riva Self Cure/HV – SDI.

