#### Interventions

3.1.7

##### Group 1

3.1.7.1

1.Initial interproximal radiography;2.Relative insulation (lip retractor, cotton roller, and saliva sucker);3.Taking the VAS scale for pain as responded by the volunteer;4.Microbiological outlet with an otoscopic curette to standardize the volume of carious tissue;5.Application—(PapacarieMblue), leave action for 20 seconds and remove the softened carious tissue just around the sidewalls of the cavity with blunt dentin spoons. Wait another 3 minutes to act on the blue dye present in the gel composition;6.Radiate with the low power laser (single point), following the parameters described in item 3.1.10;7.Clean with cotton ball and water;8.Second microbiological outlet with curette of remaining dentin tissue;9.Clinical evaluation by inspection of remaining dentin texture with rounded probe exploratory probe;10.Clean with cotton ball and water again;11.Sealing the cavity with glass ionomer cement (Riva Self Cure/HV - SDI);12.Taking VAS for Pain Responded by Volunteer;13.Preservation;14.Radiographic control 6 and 12 months.

##### Group 2

3.1.7.2

1.Initial interproximal radiography;2.Relative insulation (lip retractor, cotton roller, and saliva sucker);3.Microbiological outlet with an otoscopic curette to standardize the volume of carious tissue;4.Removal of the softened dentin dentine around the lateral walls of the cavity with sharp dentine curettes # 17;5.Second microbiological outlet with dentin curette;6.Clinical evaluation by inspecting the texture of the remaining dentin with exploratory catheter;7.Clean with cotton ball and water;8.Sealing the cavity with glass ionomer cement (Riva Self Cure/HV - SDI);9.Preservation;10.Radiographic control 6 and 12 months.

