#### Use of low-level laser for antimicrobial photodynamic therapy

3.1.10

For PDT, a low power laser will be used. The equipment Therapy XT emits red and infrared laser light. The apparatus will be calibrated according to the previous mathematical calculations to determine the parameters for antimicrobial photodynamic therapy. The laser will be applied in continuous mode, 100 mW, 2471 cm^2^, 148 J/cm^2^, irradiance 2471 mW/cm^2^, λ= 660 nm, and 6J, 60 seconds per spot. Session will be performed at the dental clinic, and at the moment of application only the volunteer to be treated and the responsible professional (operator) will be present. Specific eyewear shall be used. The active tip of the laser will be coated with clear disposable plastic (avoiding cross contamination). Based on the study by Guglielmi et al in 2011,^[15]^ the laser application will be punctual (single point) and in contact with the cavity.

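### The Group 1 procedure is described in two incompatible ways, and one adds root laser aimed at the primary outcome, so a VAS difference could not be tied to one specified procedure or to cavity aPDT alone

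*Protocol article*

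**What the plan says.** The protocol article describes the Group 1 treatment in three places.

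- **Section 3.1.7.1 (Group 1 step list).** After the gel is applied, step 5 reads "leave action for 20 seconds and remove the softened carious tissue just around the sidewalls of the cavity with blunt dentin spoons", then "Wait another 3 minutes to act on the blue dye present in the gel composition". Step 6 is "Radiate with the low power laser (single point), following the parameters described in item 3.1.10". The list has one gel application and no irradiation outside the cavity.
- **Section 3.1.9 (Experimental groups).** Of the gel it says "It will be left for 5 minutes in the cavity", and then "The carious tissue will be removed and the application of the PapacarieMblue will be repeated". The tissue is irradiated in one spot for 60 seconds with 6 J. The section adds: "These parameters were also applied in the vestibular root of the teeth, to try and prevent sensitivity". It ends with selective removal by curette, cleaning and restoration.
- **Section 3.1.10 (laser use).** It says "the laser application will be punctual (single point) and in contact with the cavity" and gives the parameters as "100 mW, 2471 cm^2^, 148 J/cm^2^, irradiance 2471 mW/cm^2", with 6 J and 60 seconds per spot. It does not mention the root.

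Section 3.1.12 makes dentin sensitivity on the VAS the primary outcome, measured before removal of carious dentin and again after the cement is placed. H1 in section 3.1.2 credits photodynamic therapy with desensitizing and decontaminating the cavities. Neither description of Group 2 includes laser on the root.

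**The concern.** Sections 3.1.7.1 and 3.1.9 cannot both be followed on the same tooth. They differ in how long the gel stays before tissue is removed, in how many times it is applied, and in whether the root is irradiated. Nothing in the article says which section governs.

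The root irradiation matters most for inference. It is given a purpose, preventing sensitivity, and sensitivity is the primary outcome. It is described for the experimental group alone. If it is delivered, the groups differ on the primary outcome by at least two things: treatment inside the cavity, and laser outside it. If it is not delivered, they differ by the first alone. The same VAS result would then support different conclusions, and a reader of the article cannot tell which applies. Replication is affected too, because two teams working from this text could deliver different treatments.

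**Working it through.** **Gel handling, side by side**

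| Item | 3.1.7.1 | 3.1.9 |
|---|---|---|
| Gel time before first removal | 20 s | 5 min = 300 s |
| Listed applications | 1 | 2 |
| Gel time after first removal | 3 min = 180 s | second application, time not stated |
| Gel time before irradiation | 20 + 180 = 200 s | 300 s + unstated time |
| Irradiated sites | single point | one spot on the tissue, plus vestibular root |
| Removal after irradiation | not listed | possibly (see below) |

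Time to first removal differs by a factor of 300 / 20 = 15. Gel time before irradiation differs by at least 300 − 200 = 100 s. One could try to reconcile the sections by treating the 3-minute wait in 3.1.7.1 as the second application in 3.1.9. That fails: the step list contains no re-application, and the first gel time would still be 20 s in one place and 300 s in the other.

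**Irradiation sites.** At 6 J per spot, a tooth receives 6 J if only the single point is treated, and 6 + 6k J if the root also receives k spots. Section 3.1.9 does not give k. For k = 1, an assumption, the total is 12 J.

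**Order of removal.** The closing sentence of the Group 1 paragraph in 3.1.9 puts selective removal after the irradiation sentences. It can be read as a further step, or as a summary of the restorative component shared with Group 2. The text does not decide between them.

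**Laser figures (3.1.10).** Inputs: power 100 mW, time 60 s, energy 6 J, irradiance 2471 mW/cm², fluence 148 J/cm², listed area 2471 cm².

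- Energy = power × time = 0.100 W × 60 s = 6.0 J, as stated.
- Fluence = irradiance × time = 2.471 W/cm² × 60 s = 148.3 J/cm², as stated.
- Area = power / irradiance = 100 / 2471 = 0.0405 cm². Cross-check: energy / fluence = 6 / 148 = 0.0405 cm².
- With the listed 2471 cm², irradiance would be 100 / 2471 = 0.040 mW/cm² and fluence 6 / 2471 = 0.0024 J/cm².

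The five other figures agree with one another. Only the area does not fit, and it repeats the irradiance number.

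**The case against.** The strongest reply is that the trial is randomized and one calibrated operator treats every tooth (3.1.3, 3.1.11). Conflicting wording does not by itself bias the comparison. This stands. A reader might infer that a VAS effect could not be attributed to anything. The documents do not support that: a difference could still be credited to the Group 1 package as delivered.

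Other parts of the reply also stand.

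- **Spot area.** A reader might infer that the impossible area leaves the laser dose open. It does not. Power, time, energy, irradiance and fluence fix the per-spot dose, so the area is a copying or unit slip.
- **Section 3.1.10.** It does not say that the cavity is the only site. Its subject is antimicrobial use, and its dose is stated per spot, so it omits the root but does not exclude it.
- **Removal after irradiation.** This is one possible reading, not a stated step.
- **12 J.** This rests on assuming one root spot.
- **Photosensitizer at the root.** None is described there. That none is used is an inference.
- **Purpose.** The general objective (3.1.1) already pairs the gel with low-power laser for desensitization, so the combined aim is partly declared. It speaks of the cavities, however, and does not settle whether the root is treated.

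One could also say that 3.1.9 merely summarizes the step list. That does not stand. A summary would say less than the list, whereas 3.1.9 gives a different time, a second application and an extra site.

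**Conclusion.** The point holds as an internal inconsistency. Sections 3.1.7.1 and 3.1.9 give incompatible Group 1 procedures: 20 s against 300 s of gel before first removal, 200 s against at least 300 s before irradiation, and one against two listed applications. Root laser appears in 3.1.9 and is not listed in 3.1.7.1 or 3.1.10. Whether removal continues after irradiation is ambiguous.

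Because the root laser is described for Group 1 only and targets the primary outcome, a VAS difference could be attributed to the package as delivered, but not to one specified procedure, nor to cavity aPDT alone as H1 has it. The loss of attribution to a component comes from the root laser. The gel conflicts affect which procedure the result describes.

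The effect on the VAS itself cannot be sized, since the article gives no expected VAS difference or standard deviation. The area figure is a minor correction. No view is taken here on which version of the procedure is right.

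**What to change.** - The investigators reconcile 3.1.7.1, 3.1.9 and 3.1.10 into one sequence of their choosing. It should fix the gel time, the number of applications with the time for each, and the place of tissue removal relative to irradiation.
- State explicitly whether the vestibular root is irradiated and, if so, how many spots.
- If the root is irradiated, word H1 and the trial's conclusion for the combined package (gel-assisted removal, cavity aPDT and root laser), not for aPDT alone.
- Minor: make the 2471 cm² entry consistent with the stated power, irradiance, fluence and energy, which together imply about 0.040 cm².

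The cost is protocol wording. If the root laser is kept, there is also a narrower claim: the trial speaks to the package and not to its antimicrobial component. Sample size, randomization and visit schedule are unaffected.

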#### Use of low-level laser for antimicrobial photodynamic therapy

3.1.10

For PDT, a low power laser will be used. The equipment Therapy XT emits red and infrared laser light. The apparatus will be calibrated according to the previous mathematical calculations to determine the parameters for antimicrobial photodynamic therapy. The laser will be applied in continuous mode, 100 mW, 2471 cm^2^, 148 J/cm^2^, irradiance 2471 mW/cm^2^, λ= 660 nm, and 6J, 60 seconds per spot. Session will be performed at the dental clinic, and at the moment of application only the volunteer to be treated and the responsible professional (operator) will be present. Specific eyewear shall be used. The active tip of the laser will be coated with clear disposable plastic (avoiding cross contamination). Based on the study by Guglielmi et al in 2011,^[15]^ the laser application will be punctual (single point) and in contact with the cavity.

#### Procedures

3.1.11

All treatments will be performed by a single operator who will be calibrated during an initial phase of the survey. An operator will perform the treatment and a pretrained examiner will assess whether removal of carious tissue did not reach the pulp. The examiner will not know to which group the participants belong. This pretrained examiner will evaluate all cavities after the respective interventions and is responsible for attesting the presence of soft dentine. The operator and the examiner must agree on the conclusion of the removal of carious dentin. This procedure will also be made in the clinical and radiographic evaluations by the previously calibrated examiners (calculation of Kappa to measure interobserver agreement above 85%).

The clinical evaluations of the complete removal of the carious tissue, microbiological and radiographic will be made by 2 blind examiners, who will not know the treatment performed on each of the teeth.

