#### General objectives

3.1.1

To investigate the application of Photodynamic Therapy (PDT) in permanent teeth with severe molar incisor hypomineralization, with painful sensitivity, associated with the presence of caries lesion. PapacárieMblue,^[28]^ modified with the addition of methylene blue as a photosensitizer, in conjunction with the low-power laser for laser therapy will be used for desensitization and decontamination of the cavities.

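### The cavity reading made right after treatment is called blind but must be agreed with the treating operator, so it is not independent and is probably not blind

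*Protocol article*

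**What the plan says.** All of the following is in the protocol article.

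- **Blinding (3.1.11 Procedures).** Of the examiner: "The examiner will not know to which group the participants belong". The closing paragraph adds that complete caries removal, microbiology and radiographs are assessments "made by 2 blind examiners, who will not know the treatment performed on each of the teeth".
- **What is read, and when (3.1.11).** "This pretrained examiner will evaluate all cavities after the respective interventions and is responsible for attesting the presence of soft dentine".
- **Agreement rule (3.1.11).** "The operator and the examiner must agree on the conclusion of the removal of carious dentin".
- **Who treats (3.1.11).** "All treatments will be performed by a single operator".
- **Dye (3.1.1 General objectives; 3.1.7.1 Group 1).** The Group 1 gel is "modified with the addition of methylene blue as a photosensitizer", and step 5 says "Wait another 3 minutes to act on the blue dye present in the gel composition". Group 2 (3.1.7.2) has no gel and no dye.
- **Texture inspection (3.1.7).** In Group 1 this is step 9, made with a rounded exploratory probe. In Group 2 it is step 6: "Clinical evaluation by inspecting the texture of the remaining dentin with exploratory catheter".

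**The concern.** Two properties are claimed for this reading, explicitly or by implication: that the examiner is unaware of the arm, and that the reading is the examiner's own. The agreement rule removes the second and weakens the first. The dye and the differing step order are further cues, and the article describes no masking of them.

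If soft dentine or completeness of removal is compared between the groups, a difference could partly reflect what the operator expected or what the examiner could see. It would nevertheless be presented as a blinded finding. Because the reading helps decide when excavation is accepted as finished, it may also affect procedure time. Under 3.1.15 the stopwatch runs until curettage is complete and the restoration is placed.

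**Working it through.** The article gives no figure on this point to reproduce, so the check sets the sections side by side.

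1. **Independence.** The single operator delivers both treatments (3.1.11) and so necessarily knows the arm. This is inferred, since the article does not call the operator unblinded. The examiner must reach agreement with that operator on the conclusion of removal. A rating that has to match the view of someone who knows the arm is not independent, whatever the examiner can see. This step needs no assumption about staining.

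2. **Sequence in each arm (3.1.7).**

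| | Group 1 | Group 2 |
|---|---|---|
| Gel with blue dye | step 5 | none |
| Laser | step 6 | none |
| Cleaning before inspection | step 7 | none listed |
| Second bacterial sample | step 8 | step 5 |
| Texture inspection | step 9 | step 6 |
| Cleaning after inspection | step 10 | step 7 |

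Group 1 is inspected between two cleanings and Group 2 before its only one. The condition of the cavity at inspection therefore differs by arm apart from the dye.

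3. **Is the dye visible?** In Group 1 the dye precedes the reading by one wipe with cotton and water and one curette sample. Section 3.1.9 describes the Group 1 sequence differently and lists curette removal after irradiation, which could take away stained tissue. On the other side, the Introduction and Discussion say that selective removal keeps soft dentine on the pulpal wall, so dye-exposed tissue may still be in view. No section reports residual colour.

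4. **How far could colour alone unmask?** Assume a share p of the 24 Group 1 cavities is visibly stained and none of the 24 in Group 2. Sorting by colour is then right in (24p + 24)/48 = (1 + p)/2 of teeth: 50% at p = 0, 75% at p = 0.5, 100% at p = 1. The documents do not give p, so the whole range is open.

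5. **Who inspects?** Section 3.1.7 does not say who makes the texture inspection. The link to the examiner comes from 3.1.11.

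6. **What depends on the reading?** The primary outcome is the child's own VAS response (3.1.12). The second bacterial sample precedes the inspection in both arms (8 before 9; 5 before 6), so as written the inspection cannot alter it. Sections 3.1.12 to 3.1.17 name no texture outcome. What remains is the reading itself and possibly procedure time.

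7. **Kappa.** Section 3.1.11 sets an interobserver kappa above 85% for the clinical and radiographic evaluations. Kappa is informative only when each rating is recorded before consensus, and the article does not state that order.

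**The case against.** The strongest defence is that this reading is a completion check. Having two people agree before a cavity is sealed is ordinary good practice, and no analysis of texture is named. In addition, 3.1.10 keeps everyone but the child and the operator out during laser application, 3.1.11 assigns the evaluation of complete removal to two blind examiners, and a condensed article may leave masking details to the full protocol.

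Much of this stands. It limits the consequences and supports keeping the agreement step for its clinical purpose. It does not remove the conflict, because the blinding claim and the agreement rule stand in the same section, and 3.1.11 itself lists complete caries removal among the blinded evaluations. Keeping the examiner away during the laser hides the laser, not the cavity read afterwards.

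A reader might also infer more than the text supports:

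- **That two different instruments are used.** Both descriptions are awkward English, and a catheter is an unlikely tool for testing dentine. A translation variant is the likelier explanation, so this is wording to reconcile.
- **That the examiner can identify the arm in most teeth.** This needs a staining rate that the documents do not give.
- **That the main outcomes are biased.** Neither the VAS nor the second bacterial count, as sequenced in 3.1.7, depends on this reading.
- **That all blinding claims fail.** Nothing here undermines the claims for microbiology or radiographs. At the later restoration checks both arms carry the same glass ionomer, so blinding there remains plausible.

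**Conclusion.** The point holds in a limited form. On the text alone, the immediate post-excavation reading is not independent, because it must be agreed with an operator who knows the arm. It is probably not blind, since only Group 1 cavities have held dye and the cleaning order differs; this part rests on the assumption that some colour remains visible. The reading is made in all 48 teeth (24 per group). The effect is confined to soft dentine and completeness of removal, and possibly procedure time. The size of any bias cannot be estimated from the documents. It is a modest flaw, worth correcting because the remedy costs almost nothing.

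**What to change.** In 3.1.11:

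- Have the examiner record the soft-dentine and completeness reading alone, before any discussion with the operator.
- Use that solo reading for any between-group report and for kappa.
- Keep the agreement step only for the decision to proceed.
- Report this immediate reading as unblinded unless the article states how the dye cue is masked. Leave the blinding claims for microbiology, radiographs and later restoration checks as they are.

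In 3.1.7, reconcile between the two arms the wording for the inspection instrument and the order of cleaning and inspection.

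The cost is one extra field on the form and some rewording, with the same examiner and the same visit. The small downside is that one assessment is openly reported as unblinded.
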